#### 2. Overall effects of the Taekwondo training program

The following assessments will be conducted by an assessor experienced in the measurement tests and blinded to group allocation at baseline, after completion of the 10-week program, and at 2-month follow-up at the university laboratory and the Taekwondo training center.

*2*.*1 Gross motor skills*. The assessment will include gross motor composites that measure manual coordination, body coordination, and strength and agility from the Bruininks–Oseretsky Test of Motor Proficiency-2 (BOT-2) [41]. Manual coordination will be evaluated through two tasks that test upper-limb coordination. Body coordination will be assessed through seven tasks that test bilateral coordination and nine tasks that test balance. Strength and agility will be evaluated through five tasks that assess running speed and agility and five tasks that evaluate strength. A trained assessor will demonstrate each item to the children during the assessment. Visual aids will be displayed on an easel for the children’s reference. The raw scores of each task will be converted to the point scores. The point scores for each task within the same gross motor composite will be added up as a sub-score. This allows for comparisons to be made across different assessment times. The BOT-2 had good test-retest reliability and internal consistency of the total scale, with an ICC of 0.99 (95% confidence interval) and Cronbach’s alpha coefficient of 0.92 [42].

*2*.*2 Taekwondo skills performance*. A scoring system was modified for use in this project with reference to the international Taekwondo referee scoring standard. This assessment will be carried out at the Taekwondo training center. Children’s performance for a set of selected Taekwondo moves and kicks will be observed and scored by two qualified referees. Both accuracy and overall presentation of the Taekwondo movement, stance, and techniques will be scored.

*2*.*3 Flanker inhibitory control and attention task from the NIH Toolbox Cognition Battery app*. The NIH Toolbox Cognition Battery app is a set of clinically validated iPad-based assessments [43]. The Flanker inhibitory control and attention task is chosen and will be used to assess the inhibitory and attentional aspects of executive function. On each trial, participants are presented with five arrows (or fish for participants under eight years old) in a horizontal line. The task is to indicate the direction of the middle arrow. Twenty trials were presented, with the flanking arrows alternating randomly between congruence and incongruence with the middle arrow. A scoring algorithm integrates accuracy and reaction time, yielding scores from 0 to 10. Total administration time is about three minutes. Test-retest reliability of this task is 0.95 (95% CI 0.92, 0.97), and correlations for convergent validity is r = 0.48 [43,44].

*2*.*4 Comprehensive trail-making test (CTMT)*. The CTMT targets to assess visual search speed, scanning, speed of processing, mental flexibility, and executive functioning. It consists of five visual search and sequencing tasks that are heavily influenced by attention, concentration, resistance to distraction, and cognitive flexibility (or set-shifting). The child is required to connect a series of stimuli (numbers, expressed as numerals or in word form, and letters) in a specified order as fast as possible in each trial. The time scores for the five CTMT trials will be converted to standardized T-scores according to the reference tables in the testing manual, and they will be summed up to produce a global performance level score, the CTMT Composite Index (CI), which can then be converted into a percentile score according to the participant’s chronological age. Higher T score and CTMT CI correspond to better performance. The CTMT has an internal consistency reliability coefficient of 0.92, and a test-retest reliability ranging from 0.70 to 0.78 [45].

*2*.*5 Social responsiveness scale*, *second edition (SRS-2)*. This scale will be completed by the parents. It is a 65-item autism rating scale widely used for identifying a spectrum of deficits in reciprocal social behavior, ranging from absent to severe, based on observations of a child’s behavior in various social settings. Scoring is on a four-point Likert scale with five subscales (social awareness, social cognition, social communication, social motivation, and autistic mannerism) [46]. Higher T-scores correspond to poorer social functioning. The questionnaire has an internal consistency of 0.95 and an inter-rater reliability of 0.77 [47].

*2*.*6 Strength and Difficulties Questionnaire (SDQ)*. The questionnaire will be completed by parents. There are 25 items in the SDQ, which consists of five scales, each with five items, for assessing children’s mental health status in terms of emotional, conduct, hyperactivity, peer problems, and prosocial behavior [48]. The questionnaire has an internal consistency coefficient of 0.81 and a test-retest reliability coefficient of 0.86 [48].

*2*.*7 Clinical global improvement (CGI) score*. The CGI-I will be completed by parents to evaluate children’s functional changes in daily life after completion of the 10-week program, and at 2-month follow-up [49]. The CGI-I consisted of 12 questions developed by our research team, which are focused on all core symptoms of ASD and covered the following aspects: (1) motor functioning; (2) children’s capability to follow instructions; (3) social, communication, and language understanding and expression; and (4) children’s capabilities for attention shifting, attention to complete a task, attention to details, and imagination. The CGI-I is rated on a 7-point Likert scale ranging from 1 (very much improved) to 7 (very much worse since the initiation of intervention), with 4 representing no change. A lower score for each item of the CGI-I indicates more favorable outcomes. In addition to these 12 questions, we modified the CGI-I in this study to include a question asking parents about the overall rating of their child and an open-ended question that enables parents to report their observations of their child after participation in this program.

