### Randomization and blinding

Block randomization will be implemented for this study, with varying block sizes of 2 to 4, to prevent selection bias and predictability. The randomisation list will be computer-generated and concealed by a researcher (author identifying information) who will have no direct contact with the participants. A research assistant will enroll participants and assign them to either the “Taekwondo training with elements of music therapy” (n = 36) or the “Taekwondo training alone” (n = 36) group in a 1:1 ratio. Given the behavioral nature of the intervention, blinding will not be feasible for the participants and parents. They will be unaware of their group allocation in the recruitment process until they provide written consent. The coaches, the trial coordinators, and the research personnel who review and code the video recording of the training sessions will also not be blinded to the group allocation. There will be concealment of the allocation sequence so that the trial coordinators will not know the group allocation of an individual before they consent them. To minimize measurement bias, all other research personnel involved in data collection, processing, and analysis will be blinded to group allocation.

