*1*.*3 Physical activity level*. Participants will also wear an optical heart rate monitor (Polar OH1Electro Oy, Kempele, Finland) [38] on their forearms to measure their exercise heart rate as a reflection of their physical activity level during the training. Continuous heart rate data will be recorded for every session and expressed as the mean heart rate per minute. The measured exercise heart rate greater than 55% and less than 70% of each individual’s maximum heart rate (estimated as 220 minus age) will be used as individualized cutoffs for moderate- and vigorous-intensity cardiovascular workload, respectively [39].

*1*.*4 Rate of perceived exertion (RPE)*. Children will be asked to rate their exertion level at regular time points at each training session using the Borg 6-to-20 Scale, in which “6” indicates “no exertion at all” and “20” indicates “maximal exertion” [40]. High test-retest reliability (r = 0.89) was found for Chinese-translated versions of the Borg 6–20 Rating of Perceived Exertion (RPE) scale, and the perceived efforts in the RPE were shown to be significantly correlated with heart rate, power output, and oxygen consumption in children (p<0.01) [34].

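### The blinded-assessor statement covers all seven programme outcomes, but SRS-2, SDQ and CGI-I, the only measures of psychosocial functioning and behaviour, are rated by parents whom the protocol says cannot be blinded

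*Protocol article*

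**What the plan says.** The section on overall effects of the programme opens with one sentence that governs everything listed under it: "The following assessments will be conducted by an assessor experienced in the measurement tests and blinded to group allocation", at baseline, after the 10-week programme and at the 2-month follow-up. Seven instruments follow: BOT-2 (2.1), Taekwondo skills (2.2), Flanker (2.3), CTMT (2.4), SRS-2 (2.5), SDQ (2.6) and CGI-I (2.7).

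The entries for the last three each name parents as the respondents. For the SDQ the wording is "The questionnaire will be completed by parents".

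Randomization and blinding says that "blinding will not be feasible for the participants and parents". On timing it says: "They will be unaware of their group allocation in the recruitment process until they provide written consent". On staff it says: "The coaches, the trial coordinators, and the research personnel who review and code the video recording of the training sessions will also not be blinded". It then adds that "all other research personnel involved in data collection, processing, and analysis will be blinded to group allocation".

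Enjoyment (CEMS) and perceived exertion (RPE) are in section 1, on immediate effects. Both are children's self-reports. CEMS is taken when each session ends. For exertion the text says: "Children will be asked to rate their exertion level at regular time points at each training session".

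**The concern.** Blinded assessment is a stated protection against bias, and a reader will rely on it when weighing the results. Here it is stated for outcomes that cannot have it. For SRS-2, SDQ and CGI-I the person making the judgement is the parent, so a blinded staff member who hands out or scores the form protects nothing.

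The three scales are the whole measurement of psychosocial functioning and behavioural problems, which the Introduction names as an outcome domain. The Discussion predicts greater improvement in social communication and behaviour in the music arm. Parents know whether their child is in the music arm or in the arm labelled as Taekwondo training alone, and may rate by expectation. CGI-I is the most exposed: it has no baseline and asks parents directly for change since the intervention began. A difference produced by expectation alone could then be read as improved social function, with no blinded measure in the same domain to set against it.

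**Working it through.** **1. Who rates each programme outcome, and can that rater be blinded?**

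| Outcome | Rater or scorer | Blinding possible under the protocol's own statements? |
|---|---|---|
| 2.1 BOT-2 | trained assessor | yes |
| 2.2 Taekwondo skills | two qualified referees | yes |
| 2.3 Flanker | assessor-administered app | yes |
| 2.4 CTMT | assessor-administered test | yes |
| 2.5 SRS-2 | parent | no |
| 2.6 SDQ | parent | no |
| 2.7 CGI-I | parent | no |

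The opening sentence is therefore untrue for 3 of 7 programme outcomes, and for 3 of 3 instruments that address psychosocial functioning and behaviour. The sentence is also inexact in a second way: it includes baseline, whereas CGI-I is collected only post-training and at follow-up.

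**2. Baseline order.** The visible text gives consent as the point until which families do not know their arm. The abstract asks only that the first assessment precede the programme. Nothing visible places baseline SRS-2 and SDQ before disclosure. Figs 1 and 3, which carry the schedule, are not shown and may settle this.

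**3. Session measures.** The list of unblinded personnel has three entries: coaches, trial coordinators and video coders. The Intervention section also places a teaching assistant and two student assistants in each session, and music is played in one arm only. Anyone who asks for RPE during a session can tell the arm. The collector is not named. If it is a coach or coordinator, the text is consistent. If it is anyone else, the statement that all other data collectors are blinded is wrong.

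**4. Illustration of consequence.** The protocol gives no figure for rating bias, so there is none to reproduce. Inputs:
- n = 36 per arm (Randomization and blinding).
- n = 29 per arm after the protocol's 20% attrition: 72 × 0.8 / 2 = 28.8.
- Two-sided alpha 0.05; true effect zero.
- Differential rating bias b, in SD units: **assumed**.

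For a two-sample t-test, the noncentrality is b × √(n/2) and the degrees of freedom are 2n − 2. For n = 36 and b = 0.2 it is 0.2 × √18 = 0.849, on 70 df with critical value 1.994. The chance of a significant result is P(|T| > 1.994) = 13.3%.

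| Assumed bias (SD) | 36 v 36 | 29 v 29 |
|---|---|---|
| 0.1 | 7.0% | 6.6% |
| 0.2 | 13.3% | 11.6% |
| 0.3 | 24.1% | 20.2% |
| 0.4 | 38.8% | 32.2% |

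A normal approximation for 36 v 36 gives nearly the same (7.1%, 13.6% and 24.7% at 0.1, 0.2 and 0.3 SD). Without bias the figure is 5%.

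**The case against.** **Loose introductory wording.** The protocol hides nothing. It says openly that parents cannot be blinded, and each of the three entries says that parents complete the form. The opening sentence fits the visit-based tests best, since it goes on to name the laboratory and the training centre. This is fair as to intent, but the sentence as written still covers 2.5 to 2.7 and should be narrowed. A reader might infer that the trial report will present these scales as blinded; that is a prediction, and the documents do not say it.

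**Enjoyment and exertion.** A reader might infer that the protocol also claims blinded assessment for CEMS and RPE. It does not. The opening sentence covers section 2 only, the children rate themselves, and children are declared unblinded. Audible music is a reasonable inference for RPE within the session, but nothing says that it is playing when CEMS is taken. Only the question of who collects them remains.

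**Baseline order.** A reader might infer that baseline questionnaires are completed after disclosure. The text permits this but does not say it, and the schedule figures are not available. It supports a safeguard, not a finding of error.

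**Size.** Both arms receive the same Taekwondo level, skills and duration, so the difference in parents' expectations may be small. The planned analysis of the before-and-after scales is an adjusted mixed model, not a simple two-group comparison. Both points stand, and the percentages can only illustrate.

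**CGI-I is broader than behaviour.** It also asks about motor function, following instructions and attention, and motor function and attention have assessor-administered measures. That is correct, but it adds no blinded measure of social or behavioural function.

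**Weight.** Only secondary outcomes are affected. The primary outcome, engagement, lies outside this point.

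**Conclusion.** The point holds for SRS-2, SDQ and CGI-I, and this rests on the text alone: the protocol states a protection that three of its seven programme outcomes, including every measure of psychosocial functioning and behaviour, do not have. The other four can be blinded as described.

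The size of any bias is unknown. Under an assumed differential of 0.2 to 0.4 SD and no true effect, false-positive results would occur in 13% to 39% of trials with 36 per arm, and in about 7% at 0.1 SD. This is a what-if calculation for a simple two-group test and does not estimate the trial's actual error rate.

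The baseline order is a precaution that depends on figures not shown. The RPE and CEMS collectors need clarification only. The matter should be corrected because it governs what the trial may conclude about social function and behaviour, but it does not threaten the primary result.

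**What to change.** 1. In the section on overall effects, limit the blinded-assessor statement to BOT-2, Taekwondo skills, Flanker and CTMT. State that SRS-2, SDQ and CGI-I are unblinded parent reports.
2. State in advance that a benefit seen only on these three scales will be reported as parent-perceived, and not as evidence of improved social function or behaviour.
3. If the schedule figures do not already ensure it, specify that baseline SRS-2 and SDQ are completed before families learn their allocation.
4. In Randomization and blinding, name who collects RPE and CEMS and list them as unblinded. No change to how the music is used is needed: silencing it for each rating would interrupt the intervention and still not blind the child, who is the rater.

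The cost is a few sentences and, at most, the order of two existing steps. Items 1 and 2 do not reduce the bias itself, because parents remain unblinded; they make the claim match the evidence. The downside is a weaker claim on the psychosocial outcomes.

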### Statistical analysis

The participants’ characteristics and primary and secondary outcomes will be evaluated using summary statistics, including mean (SD), median (IQR), or proportions as appropriate, at multiple time points. The primary analysis will consist of an intention-to-treat analysis comparing the primary outcome (engagement) between the two intervention groups; specifically, a linear mixed-effect model will be used to investigate the effect of intervention (Taekwondo training with vs without elements of music therapy) over time (interaction between intervention and time) on the engagement in the training sessions, with a random effect for each participant. The effects of music therapy on the secondary outcomes measured during the training sessions, including physical activity levels, enjoyment state, and the rate of perceived exertion, will be tested by independent samples t-tests. Further, we will use a linear regression model to investigate the effect of intervention on these outcomes, adjusting for the following prognostic variables: age, sex, and BMI. A log transformation will be applied for any outcomes resulting in a skewed distribution.

For the other secondary outcomes measured before and after the training sessions, a linear mixed-effect model will be used to investigate the effect of intervention over time (interaction between intervention and time), with a random effect for each participantand adjusting for the following prognostic variables: age, sex, and BMI. The analyses will also evaluate the sustained benefits of the training by assessing the effect of the intervention on the secondary outcomes at the 2-month follow-up using the statistical methods described above. The significance level will be set at *p*< .05, and all analyses will be performed using SPSS (v25.0 for Windows; IBM, Armonk, NY, USA).

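### The CGI-I has no usable baseline, and the only model named for programme-level secondary outcomes, an intervention-by-time interaction, would test decay between its two visits rather than benefit

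*Protocol article*

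**What the plan says.** Three places in the protocol article bear on this.

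- **Lead-in to section 2 (Overall effects of the Taekwondo training program).** The assessments that follow, numbered 2.1 to 2.7, are to be made by an experienced assessor "blinded to group allocation at baseline, after completion of the 10-week program, and at 2-month follow-up". The CGI-I is item 2.7.
- **Section 2.7 (CGI score).** The timing is stated separately: "The CGI-I will be completed by parents to evaluate children’s functional changes in daily life after completion of the 10-week program, and at 2-month follow-up". No baseline occasion is given. Items are scored on seven points, "ranging from 1 (very much improved) to 7 (very much worse since the initiation of intervention), with 4 representing no change", and lower is better.
- **Statistical analysis.** Physical activity, enjoyment and perceived exertion, all measured within sessions, get t-tests and linear regression. Then: "For the other secondary outcomes measured before and after the training sessions, a linear mixed-effect model will be used to investigate the effect of intervention". The effect of interest there is the interaction of intervention with time, with a random effect for each participant and adjustment for age, sex and BMI. Sustained benefit is to be judged by "assessing the effect of the intervention on the secondary outcomes at the 2-month follow-up using the statistical methods described above".

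**The concern.** The two schedules disagree on whether the CGI-I is taken at baseline, and the nature of the scale decides which one can work: a rating of change since the start has nothing to report before the start.

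The analysis text then leaves the instrument without a home. It is not a within-session outcome, so the t-test and regression do not cover it. It has no pre-training value, so it does not meet the description of the outcomes given the mixed model. Yet the sentence on the 2-month follow-up carries the same methods to the secondary outcomes without excepting the CGI-I.

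For an ordinary pre/post outcome the interaction is the treatment effect, because the arms are expected to be equal at baseline. For a score that is already a change, the arm difference at each visit is the treatment effect. An analyst who follows the named method on the two available visits would be testing something else, and a lasting improvement in daily functioning could go undetected.

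**Working it through.** **Inputs.** Two CGI-I visits (section 2.7); 36 children per arm (Randomization and blinding); significance level 0.05 (Statistical analysis), taken as two-sided. The protocol gives no effect size, power or error rate for the CGI-I, so there is no figure of its own to reproduce. For illustration I borrow d = 0.55 from the sample size section, where it is stated for engagement; it follows from 11.8/21.6 = 0.546. I add d = 0.8 as a second value. The correlation rho between the two visits is an assumption, varied from 0.3 to 0.9. Children are treated as independent, data as complete, and covariates are left out.

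**Step 1: what the interaction estimates.** Let D0, D1 and D2 be the mean difference (music minus no music) at baseline, post-training and 2 months.

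- Ordinary pre/post outcome: interaction at post-training = D1 − D0. Randomisation makes the expected D0 zero, so this equals D1, the treatment effect.
- CGI-I with its two visits: interaction = D2 − D1. Write a benefit of size b as D1 = −b, since lower is better.
  - Benefit fully kept: D2 = −b, so the interaction is −b − (−b) = 0.
  - Benefit entirely lost: D2 = 0, so the interaction is 0 − (−b) = +b.

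The test is therefore silent when the benefit lasts and signals when it disappears. The first result does not depend on b or on rho.

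**Step 2: rejection rate of that interaction under a sustained benefit.** With two visits and complete data, the random-intercept interaction test is a t-test on each child's change between visits. Its expected value is zero, so it rejects at the significance level. Simulation with 10,000 trials per setting gave 4.7% to 5.3% for d = 0.55 and d = 0.8 across the correlations tried.

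**Step 3: power of a direct arm comparison at one visit.** Noncentrality = d × sqrt(n/2), with 2n − 2 degrees of freedom.

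- n = 36, d = 0.55: 0.55 × sqrt(18) = 2.33 on 70 df, power 0.63.
- n = 27 (half of the protocol's minimum of 54), d = 0.55: 0.55 × sqrt(13.5) = 2.02 on 52 df, power 0.51.
- d = 0.8, by simulation: about 0.92 with 36 per arm and 0.82 with 27 per arm.

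| Sustained benefit, 36 per arm | Interaction on two visits | Arm difference at one visit |
|---|---|---|
| d = 0.55 | about 5% | about 63% |
| d = 0.8 | about 5% | about 92% |

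**The case against.** **The specific section governs.** The lead-in is loose as a description of the whole section: it speaks of a trained, blinded assessor, while the SRS-2, SDQ and CGI-I are completed by parents. Section 2.7 gives its own timing, which suits the scale, and the schedule figures are not available to check. This largely stands; the schedule conflict alone is a wording matter. But the 2.7 timing is exactly the one under which the interaction says nothing about benefit.

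**The model may not apply to the CGI-I at all.** Its sentence is limited to outcomes with a pre-training measurement, so the CGI-I may simply have no analysis named in the article, and a full analysis plan could supply one. This is a fair reading. It does not clear the point entirely, because the lead-in says a baseline is taken and the follow-up sentence extends the same methods to the secondary outcomes generally.

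**A sustained benefit need not be reported as no effect.** A reader might infer that it certainly would be. The documents do not support that: the follow-up sentence aims at an intervention effect at 2 months, and a model with arm, visit and interaction terms can also give the arm contrast at each visit. The 5% figure applies only if the two-visit interaction is the result relied on.

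**The baseline could be filled with a constant 4.** A reader might infer from the lead-in that every child would be entered as unchanged at baseline and that the model's standard error would then be wrong. Nothing in the protocol says a 4 would be entered. Even if it were, the ratio of model to true standard error for the post-training contrast would be sqrt(2(2 − rho)/3): 1.065 at rho 0.3, exactly 1 at 0.5 and 0.93 at 0.7. The error is conservative below 0.5 and anti-conservative only above it, so no general claim follows.

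**Conclusion.** The point holds as a minor one. The section 2 lead-in, section 2.7 and the Statistical analysis section do not fit together for the CGI-I. Read literally, the scale has no suitable analysis. Read broadly, it is given a test of decay between visits. Under that broad reading a fully kept benefit has an expected interaction of zero, which is algebra and rests on no assumed effect or correlation.

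The contrast with about 63% power does rest on assumptions: d = 0.55 transferred from engagement, 36 children per arm with complete data, independent observations and no covariate adjustment. It shows what the direct comparison could offer; it is not a forecast for this scale.

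One secondary outcome is affected. The primary analysis of engagement does not change, and the SRS-2 and SDQ, also parent-reported, have no comparable obstacle to a baseline score.

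**What to change.** Reconcile the three places:

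1. In the section 2 lead-in, except the CGI-I from the baseline visit, in line with section 2.7.
2. In Statistical analysis, state that the CGI-I is not tested by the intervention-by-time interaction. Its intervention effect is the between-arm difference at post-training, and the between-arm difference at 2 months is the sustained effect.
3. Estimate both from one model of the two visits with arm, visit and arm-by-visit terms, keeping the planned adjustment for age, sex and BMI. Report the arm contrast at each visit and use the interaction only to describe decay.

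The cost is a few sentences of wording. No new data or participants are needed, and a baseline form is dropped if one had been planned. The wording should be settled before outcome data are examined by arm, so that the definition of the CGI-I effect is not chosen after seeing results.
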